### Intervention

The PI/JP curriculum aims to develop strong parenting practices and facilitate relationship-building between parents and youth, while emphasizing Latino cultural values, navigation in multiple cultures, and environmental risks related to socioeconomic circumstances. As outlined in Table
3, the curriculum is comprised of eight 3-hour sessions including 30 minutes for dinner and conversation to facilitate social support among parents. Four sessions include parents only, one session includes parents and youth in independent topics, and three sessions include parents and youth in parallel topics with joint skill-building sessions at the end. All sessions are learner focused and follow an experiential learning approach, integrating participants’ reflections, didactics, skill-building activities, and group discussions.

**Table 3 T3:** Description of the intervention sessions

**Session**	**Participants**	**Goals for the session**	**Example activities**
1 Parenting Styles	Parents	Parents will:	Parents will:
		· Recognize their own parenting style.	· Review a video on parenting styles and discuss.
		· Distinguish the key elements of the positive parenting style.	· Self-assess their parenting styles and discuss in small groups.
2 Between Multiple Worlds	Parents	Parents will:	Parents will:
		· Recognize that their strong family orientation as Latino parents protects against youth risk behavior.	· Identify their own cultural values as parents and compare/contrast with those of school and youth.
		· Understand that their youth must navigate between family, school, and peer cultures.	· Self-assess their own and their youth’s cultural orientation and reflect on differences.
		· Learn skills to help their youth navigate across cultures.	
3 Adolescent Development	Parents	Parents will:	Parents will:
		· Review normal adolescent development and the need to adapt parenting strategies to developmental stages.	· Compare the behaviors of their youth with previous years.
		· Contextualize challenging behavior within tasks of adolescent development.	· Reflect on why adolescents challenge parents and how not to ‘take it personally’.
4 Communication	Parents and youth	Parents will:	Parents will:
		· Understand how strong communication fits with the values of respect for authority and *confianza* (trusting relationships).	· Practice active listening.
			· Discuss barriers and facilitators to conversations with youth.
		· Learn basic principles of good communication and develop communication skills.	· Practice communication using ‘I’ messages.
		Youth will:	Youth will:
		· Recognize the importance of communication with parents.	· Play the broken phone and identify barriers in communication.
		· Learn specific communication skills.	· Practice when and how to talk and listen.
			· Practice ‘I’ messages.
5 Discipline	Parents	Parents will:	Parents will:
		· Learn the importance of positive behavioral reinforcement.	· Identify strategies to encourage positive behavior in their youth.
		· Understand the importance of establishing negotiable and non-negotiable rules, and establishing and reinforcing consequences.	· Practice developing negotiable and non-negotiable rules for their family.
6 Conflict resolution	Parents and youth	Parents will:	Parents will:
		· Understand that conflict is part of the normal developmental process, and does not need to damage their relationships.	· Identify positive and negative aspects of conflicts.
		· Identify collaborative problem-solving and conflict resolution strategies.	· Discuss and role-play a strategy to solve problems with their youth.
		· Learn to recognize and self-regulate emotions.	· Develop strategies to manage anger.
		Youth will:	Youth will:
		· Learn collaborative problem-solving strategies.	· Talk about rules, consequences and mistakes.
		· Identify strategies to recognize and manage emotions.	· Talk about emotions and their consequences.
			· Name the steps to effectively solve problems.
7 Supervision and Friends’ Influence	Parents and youth	Parents will:	Parents will:
		· Understand the meaning and importance of monitoring.	· Discuss scenarios to differentiate supervision from over-control.
		· Learn strategies to monitor their youth effectively at each developmental stage of adolescence.	· Role-play initiating conversations with parents of their children’s friends.
		Youth will:	Youth will:
		· Identify dreams that they want to achieve.	· Develop a collage to help visualize dreams and goals.
		· Identify influences and behavior (including substance use) that may get in the way of achieving dreams.	· Practice strategies to refuse risky behaviors.
		· Learn strategies to avoid problem behaviors.	
8 Connection	Parents and youth	Parents will:	Parents will:
		· Understand that parent–youth connection is the foundation for parenting, and recognize barriers to relationship-building.	· Engage in activity around setting kids as priority for time.
		· Identify strategies to strengthen their relationship with their youth.	· Write a letter to their children expressing their love and expectations.
		Youth will:	Youth will:
		· Reflect on the importance of a strong parent–youth relation.	· Complete a map of personal connections.
		· Identify parents and other adults as a support network.	· Write a message to their parents expressing their thankfulness.

Each parent session will begin with identification of a challenge the parent has experienced in the last week with their youth related to the topic of the day. The intent of this exercise is to ground the didactic and skill-building materials in a problem relevant to the family’s current situation. Facilitators will then ask parents to reflect on their own topic-specific experiences as a youth to generate empathy in the parents for their children’s situations and challenges. The remainder of the session will focus on a combination of presentation of didactic information, sharing, and skill-building exercises. The skill-building exercises largely use tobacco and other substance use as examples, thus infusing all sessions with practical means for preventing substance use. The sessions end with parents reflecting on how the information and skills they learned may be applied to the challenge with their youth they identified at the beginning of the session. Parents then set an achievable goal for the week to address this challenge, and at the beginning of the following session share their experiences implementing this goal.

Youth sessions begin with an icebreaker activity and a debriefing period that introduces the day’s topic with the dual intent of cultivating a youth-friendly atmosphere and also metaphorically relating the topic of the day to a concrete idea. Introduction of new concepts follows, intermingled with a variety of theme-related activities, skill-building exercises and role-playing, helping to solidify the proposed topic of the day. The youth curriculum was formatted to rotate between didactic moments, key conversations, and activities in order to be continuously engaging and appropriately meeting the youth’s needs as adolescent learners.

Sessions using the parallel parent–youth format are communication, conflict resolution, and connection. Involving youth in the relationship-oriented sessions is intended to invest both parents and youth in building solid relationships that facilitate successful parenting practices
[19]. For these sessions, parents and youth initially meet independently. The two groups will come together at the end of the sessions for joint skill-building exercises and discussion. For the parent–youth session without joint activities, parents will focus on parental monitoring while youth will build basic youth social competencies such as goal-setting, and refusal skills that have been associated with lower tobacco and other substance use behaviors
[52,53].

Because the proposed program was developed in collaboration with community agencies, the likelihood of close adherence to the intervention protocol is high. However, fidelity will be assured through extensive training, observation of training, and delivery of structured feedback for facilitators delivering the intervention. A detailed checklist addressing implementation factors will be used to evaluate fidelity, including appropriate delivery of key content for each session, and utilization of study materials. All sessions will be videotaped and a random selection of 40% of the session tapes representative of all sites will be reviewed using the checklist. Summary fidelity scores will be generated for each implementation factor.

### Statistical analyses

#### Sample size and power

Baseline susceptibility rates of 22% for both groups and a 6-month absolute increase of 6% in the control group are consistent with susceptibility rates and likelihood of tobacco use rates observed in other studies for youth in this age range
[24,36,54]. We will anticipate a post-intervention absolute decrease of 14% in the likelihood of youth tobacco use
[24]. Using a conservative estimate of an 8% decrease in smoking intention in the intervention group, compared with a 6% increase in the control group at 6 months, a sample size of 140 per group provides 80% power to detect this difference as significant using a two-tailed chi-square test of proportions with significance level (alpha) of 0.05. Anticipating a loss to follow-up of 18%, we will initially enroll and randomize 336 families. A difference ≥0.20 in mean pre/post changes in parenting behavior scores represents a difference comparable with those found in evidence-based programs listed on SAMHSA’S national registry,
[55,56] and is consistent with differences observed in the feasibility study.

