## Background

The American Cancer Society has described cigarette smoking as the most preventable cause of premature death in the United States
[1]. While smoking rates have declined among youth in the US over recent years, in 2005 one-half of all youth had tried cigarettes by the 12th grade
[2]. Further, point prevalence data indicate that 8% of middle school students and 23% of high school students are current smokers
[3]. Alcohol and illicit drug use have also decreased in recent years, but again remain at unacceptably high rates. That is, 75% of students have consumed more than a few sips of alcohol, and one-half have tried an illicit drug by the end of high school
[2].

National data suggest that, compared with whites, middle-school-aged Latino adolescents are at equal or increased risk for lifetime tobacco, alcohol, marijuana, and other illicit drug use
[2,4]. However, considering that the majority of Latino youth are first or second generation
[5], and that rates of tobacco, alcohol, and other drug use increase in Latino youth with greater time in the US
[6-8], rates of tobacco and other substance use will probably rise in future years without prevention efforts.

Protective effects against tobacco and other substance use seen in immigrant adolescents may be conferred by the norms, values, and behaviors that their parents bring from their countries of origin. For example, researchers have identified the traditional Latino value of familism – belief in the importance of family, including extended family
[9] – as protective against alcohol use in youth
[6,10]. Broader research on adolescent health suggests that parents have an important impact on their health behaviors
[11], particularly among ethnic diverse groups
[12,13]. Relationship characteristics, such as warmth, support, and acceptance, and parenting practices such as monitoring, discipline, and positive communication, protect against future tobacco, alcohol, and illicit drug use
[11,14,15], and may be even stronger predictors of substance use for adolescents from diverse ethnicities
[16]. However the quality of relationships and parenting practices are affected by immigration factors, which in turn affect youth substance use
[17,18].

Because characteristics of the parent–youth relationship and parenting practices are associated with tobacco and other substance use outcomes, these family factors are common targets of parent training interventions

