**Exclusion criteria**	
	Mental disorder incompatible with the participation on the trial
	Prior participation in Padres Informados/Jóvenes Preparados pilot or planning

The primary outcome is intention to use cigarettes in the participating youth, which will be operationalized as susceptibility to smoking assessed among never-smokers and puffers from their responses to three questions (never-smokers) or two questions (puffers)
[35,36]. These questions are: ‘Do you think you will try a cigarette soon?’ (not asked of puffers), ‘Do you think you will be smoking cigarettes one year from now?’, and ‘If one of your best friends were to offer you a cigarette, would you smoke it?’ A never-smoker will be considered nonsusceptible if the answer to the first question is ‘no’ and answers to the both the second and third questions are ‘definitely not’; a puffer will be considered nonsusceptible if answers to the second and third questions are ‘definitely not’. Additional outcomes of alcohol, marijuana and other substance intentions, and past 30-day use of all substances will be assessed through items previously used with middle-school-aged Latino youth
[37,38]. Secondary outcomes include parenting practice and parent–youth interpersonal relational measures that are known to be important predictors of substance use among youth. Table
2 presents the instruments used to evaluate each outcome. We chose scales with established reliability and validity, availability in Spanish, and that were appropriate for low-literacy groups. Most scales include parallel items to be completed by both parents and youth. Bilingual data collectors will lead group interviews using paper-and-pencil surveys with adults and self-administered computer-assisted survey interviewing with youth.

**Table 2 T2:** Instruments used to measure parenting practices and parent–youth relationships

**Scale**	**Cronbach’s alpha in Mexican/Latino population (reference)**
Parenting practices	
Parental Monitoring Knowledge	0.78 to 0.82 [39-41]
Parental Acceptance	0.67 to 0.79 [42]
Consistent Discipline	0.69 to 0.77 [43]
Parenting Practices Self-efficacy	0.86 to 0.94 [44]
Multidimensional Scale of Perceived Social Support	0.93 to 0.86 [45-49]
Parent–youth relationships	
Parent**–**Youth Positive Attachment	0.81 to 0.85 [50]
Adolescent Parent–Child Conflict/Conflict Processes	0.87 to 0.92 [51]

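### Enrolling 336 families with 18% loss leaves about 138 youth per group, not 140, and nothing is allowed for eligible smokers whom the primary outcome cannot score

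*Protocol article*

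**What the plan says.** All of this is in the Protocol article.

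- **Assumed rates (Sample size and power).** The starting point is "Baseline susceptibility rates of 22% for both groups and a 6-month absolute increase of 6% in the control group". The intervention arm is planned as follows: "Using a conservative estimate of an 8% decrease in smoking intention in the intervention group". The 6-month rates implied are 28% (control) and 14% (intervention), although neither is written out.
- **Test and size (same section).** The test is a "two-tailed chi-square test of proportions with significance level (alpha) of 0.05", and "a sample size of 140 per group provides 80% power to detect this difference".
- **Enrolment (same section).** "Anticipating a loss to follow-up of 18%, we will initially enroll and randomize 336 families". No other allowance is made.
- **Primary outcome (Design overview, text after Table 1).** It is "susceptibility to smoking assessed among never-smokers and puffers", with three questions for the first category and two for the second. No category exists for youth who smoke more than that.
- **Eligibility (Table 1).** The youth criteria are age, language, Latino identity and assent. The exclusions are an incompatible mental disorder and earlier involvement in the pilot or planning. Smoking status appears in neither list.
- **Analysis set (Missing data strategies).** The primary logistic regression uses only youth who have a susceptibility response at 6 months, and the outcome is not imputed.

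**The concern.** Two things do not fit together.

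First, the enrolment number does not follow from the stated loss rate and the stated number required per group.

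Second, the article fixes who may enter, whom the primary outcome can score, and how many families are enrolled, and these three statements conflict. A youth who smokes beyond puffing may be enrolled and randomised, may attend the 6-month visit, and still have no defined value of the primary outcome. Such a youth is not lost to follow-up, so the 18% does not cover the case.

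What is at stake is mainly that the stated evaluable number is not what the design yields. A related consequence concerns bias rather than power: a youth who progresses to smoking during the trial would leave the primary comparison after randomisation, because of the very behaviour the programme is meant to prevent.

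**Working it through.** **Inputs from the document.** Two-sided alpha 0.05; 22% + 6 = 28% in control; 22% − 8 = 14% in intervention; 140 per group (280 in total); 18% loss; 336 families with one youth each, so 168 per group with equal allocation.

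**Input that is an assumption.** The share *s* of followed-up youth who smoke beyond puffing and cannot be scored. The article gives none for this trial, so a range is used.

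**1. Reproducing 140 per group.** Pooled two-proportion formula without continuity correction, with difference d = 0.14 and mean rate 0.21:

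n = [1.960·√(2·0.21·0.79) + 0.842·√(0.28·0.72 + 0.14·0.86)]² / 0.14² = (1.129 + 0.478)² / 0.0196 ≈ 131.7, so 132 per group.

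Power at n per group is Φ[(0.14·√n − 1.129) / 0.567]. At n = 140 this gives 82.4%. With a continuity correction the requirement is 146 per group and power at 140 is 78.3%. The two methods bracket the stated 140 and 80%, so the planned size is reasonable for 28% versus 14%.

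**2. Enrolment.**

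- 336 × 0.82 = 275.5, or 137.8 per group.
- The loss that 336 does accommodate: 1 − 280/336 = 16.7% (336 = 280 × 1.2).
- The number that 18% loss would need: 280/0.82 = 341.5, so 342.

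The gap is 6 families in 342 (1.8%), or about two youth per group. Power at 138 is 81.8%, which is 0.6 point below the value at 140.

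**3. Adding unscorable youth.** Evaluable per group = 168 × 0.82 × (1 − s) = 137.76 × (1 − s):

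| Assumed s | Evaluable per group | Power, 28% v 14% |
|---|---|---|
| 0% | 137.8 | 81.8% |
| 3% | 133.6 | 80.6% |
| 5% | 130.9 | 79.8% |
| 8% | 126.7 | 78.5% |

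The break-even share is 1 − 131.7/137.76 = 4.4%, so power is below 80% from roughly 5%.

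**4. Effect that is powered.** Odds ratio = (0.14/0.86) / (0.28/0.72) = 0.42.

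**The case against.** The strongest reply is that very little power is lost. The named test needs only 132 per group, so the 138 left after 18% loss still carry 81.8%. This stands. A reader might infer from the mismatch that the loss rate itself takes away the claimed 80% power; the figures do not support that.

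A reader might also point to continuity-corrected power, which is 77.6% at 138. But it is already 78.3% at 140, so that deficit comes from the choice of formula, not from enrolment or attrition. The plan names no correction.

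Next, the share of unscorable youth is unknown. The upper end of the range borrows the Background figure, "8% of middle school students and 23% of high school students are current smokers". That is national current smoking, not smoking beyond puffing. The trial enrols 10- to 14-year-olds with a parent born in Latin America, and the Background itself describes protective influences in immigrant families. The 8% is therefore an illustration and not a forecast. At 3%, power remains above 80%.

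It may also be tempting to say that the planned effect is wrongly called conservative, since 8 + 6 equals the 14-point decrease the article anticipates. That holds only if the anticipated 14% is a between-group difference. If the 14% and the 8% are both within-arm changes, 8 is smaller than 14 and the word is right. The document does not settle which is meant.

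Finally, an article condenses a fuller protocol, which may contain a scoring rule for smokers. Even so, the article states the outcome definition, the eligibility and the enrolment calculation itself, and as stated they do not agree. The planned sensitivity analyses for attrition do not assign an outcome to a youth who attends but cannot be scored.

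**Conclusion.** The point holds in a limited form. The stated enrolment and loss rate give about 138 evaluable youth per group, not 140. Taken alone this is a small inconsistency that costs about half a point of power. The allowance also omits a source of loss that the article's own definitions create, because smokers beyond puffing are eligible but have no primary outcome value. Under an assumed 3% to 8% unscorable, the design yields about 134 to 127 per group and about 80.6% to 78.5% power.

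These figures assume equal allocation, the uncorrected chi-square test, true rates of 28% and 14%, and the same unscorable share in both groups among those followed up. They do not show that the trial is materially underpowered. They show that the stated evaluable number is not the one delivered, and that the missing scoring rule should be settled for the integrity of the randomised comparison more than for power.

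**What to change.** 1. Make the enrolment sentence consistent: either give the loss rate as 16.7%, or keep 18% and state about 138 evaluable youth per group.
2. State how youth who smoke beyond puffing are scored at 6 months. One option is to count them as susceptible, which keeps them in the randomised comparison. Otherwise, restate the evaluable number and power for scorable youth only, giving the assumed share and its range.
3. Write out the assumed 6-month rates (28% control, 14% intervention, odds ratio 0.42), so that the size can be checked directly.

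The cost is a few restated figures and one scoring rule. No additional families are required.

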#### Data analysis

The primary outcome, susceptibility to smoke cigarettes, will be evaluated by a multiple logistic regression model to generate an adjusted odds ratio testing the null hypothesis that the 6-month post-intervention susceptibility rate is the same in both groups. The 6-month post-intervention susceptibility to use other substances also will be compared between intervention and control groups.

Mixed-effect models utilizing repeated measures of smoking susceptibility, and including intervention as a time-varying covariate, will be used to evaluate intervention effects on growth trajectories of susceptibility to smoking. Both linear and nonlinear models will be explored to identify the most appropriate characterizations of changes over time in susceptibility to smoking for each group.

The secondary outcomes, self-reported parenting practices and parent–youth interpersonal relations, will be evaluated by analysis of covariance models. In addition, within-group changes over time in mean parenting and relationship scale scores will be assessed using repeated-measures analysis of variance.

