**Figure 1 F1:**
[figure not shown]
**Padres Informados/Jóvenes Preparados conceptual model.** *Intervention components in gray.

The community collaborative board was expanded to include seven participating community agencies: five urban and two rural agencies, including two clinics, a school, three social service agencies and a University of Minnesota Extension site. Agencies serve a largely Latino constituency and hold reputations as trusted service providers. All agencies agreed to participate in the planning, implementation, and evaluation of the project as is consistent with CBPR principles
[33].

The study will proceed through a planning and training phase (year 1), a serial implementation phase (years 2 to 4), and a data analysis and dissemination phase (year 5). To increase community capacity for supporting family-skills training and participating in future research collaborations, collaborating agencies are responsible for recruitment of participants and delivery of the intervention. Therefore, each collaborative site will select two staff to directly participate in the project: one to recruit and coordinate program activities, and a second to deliver the intervention. Community collaborators will be prepared for their roles through extensive training in protection of research participants’ confidentiality, the content of the program, and the theoretical background and practical skills needed for intervention implementation. Criteria for site-facilitators who will deliver the intervention include: preference for degree in education, psychology/therapy, or social work, but left to the discretion of site; at least 3 years of experience providing direct service to Latino families; and bicultural and bilingual in English/Spanish.

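### Group training in the intervention arm is ignored by the power calculation and the primary logistic model; any within-group correlation makes the standard error too small and power lower than stated

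*Protocol article*

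**What the plan says.** Under Design overview, the family is the unit of randomisation, 336 families are to be enrolled from seven agencies, and control families are trained about six months after the intervention families.

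Delivery is in groups. Each agency selects two staff (Methods/Design, after Figure 1): "one to recruit and coordinate program activities, and a second to deliver the intervention". The Intervention section describes group discussion, sharing of weekly challenges and goals, parent and youth groups that join for skill-building, and "30 minutes for dinner and conversation to facilitate social support among parents".

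On power, the Sample size and power section states that "a sample size of 140 per group provides 80% power to detect this difference as significant using a two-tailed chi-square test of proportions", at a two-sided 5% level. The only allowance added is for 18% loss to follow-up.

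On analysis, the Data analysis section says the primary outcome "will be evaluated by a multiple logistic regression model to generate an adjusted odds ratio". The adjustment covariates are not listed. The mixed-effect models in the same section are for repeated measures of susceptibility over time, not for training groups. The secondary scales are analysed by covariance models.

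**The concern.** This is a partially nested design: one arm is formed into groups after individual randomisation and the other is not. Families who share a facilitator, discussion and role-play may come to resemble one another in outcome. The Discussion itself expects delivery to vary, since it warns that facilitators with differing experience may lower fidelity.

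That variation adds a between-group component to the variance of the intervention arm. A chi-square test or a standard logistic regression leaves it out. At stake is the primary efficacy claim: a p-value just under 0.05 could owe its significance to variance that was not counted, and the trial could have less power than its sponsor believes.

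**Working it through.** **Inputs from Sample size and power.** Baseline and control change: "Baseline susceptibility rates of 22% for both groups and a 6-month absolute increase of 6% in the control group", so the control rate at six months is 22% + 6% = 28%. Intervention change: "Using a conservative estimate of an 8% decrease in smoking intention in the intervention group, compared with a 6% increase in the control group", so the intervention rate is 22% − 8% = 14%. The mean of the two is 21%.

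**The plan's own figure.** With 140 per arm and independent families:
- SE under the null = √(2 × 0.21 × 0.79 / 140) = 0.0487
- SE under the alternative = √((0.28 × 0.72 + 0.14 × 0.86) / 140) = 0.0480
- Power = Φ((0.14 − 1.96 × 0.0487) / 0.0480) = 82.4%

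With a continuity correction power is 78.3% (79.0% by exact enumeration). The number needed for 80% is 132 per arm uncorrected and 146 corrected. The stated 80% therefore sits where an independent-families calculation puts it, with no design effect built in.

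**Analysed number.** 336 × 0.82 / 2 = 137.8, or about 138 per arm. Uncorrected power with no clustering is then 81.8%.

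**Group size (assumed; not in the article).** 336 / 7 = 48 families per agency and 24 per arm. Two groups of 12 per agency, less 18% attrition, leave 12 × 0.82 ≈ 9.8 analysed families per group. Attrition has to be applied to the group size as well as to the arm.

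**Clustering in the intervention arm only.** This takes control families as untrained at the primary comparison. With group size m:
- DE = 1 + (m − 1) × ICC
- True SE relative to naive SE under the null = √((1 + DE) / 2)
- Type I error of the naive test = 2 × (1 − Φ(1.96 / √((1 + DE) / 2)))
- Power of a correct test = Φ((0.14 − 1.96 × SE₀) / SE₁), where SE₀² = 0.21 × 0.79 × (1 + DE) / 138 and SE₁² = (0.28 × 0.72 + DE × 0.14 × 0.86) / 138

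Worked case, ICC 0.05: DE = 1 + 8.8 × 0.05 = 1.44. SE₀ = 0.0542 and SE₁ = 0.0521. Type I error = 2 × (1 − Φ(1.96 / 1.105)) = 7.6%, and power = 74.2%.

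| ICC (assumed) | DE | True/naive SE, null | Naive type I error | Power, 138 per arm |
|---|---|---|---|---|
| 0 | 1.00 | 1.00 | 5.0% | 81.8% |
| 0.01 | 1.09 | 1.02 | 5.5% | 80.3% |
| 0.02 | 1.18 | 1.04 | 6.0% | 78.7% |
| 0.05 | 1.44 | 1.10 | 7.6% | 74.2% |

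**Wider range.** With m = 6 and ICC 0.01, type I error is 5.3% and power 80.9%. With m = 20 and ICC 0.05, they are 10.7% and 66.1%. At 138 per arm, uncorrected power drops below 80% once DE reaches about 1.10, which at m = 9.8 is an ICC of about 0.10 / 8.8 ≈ 0.012.

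**The case against.** **The harm is conditional.** Neither ICC nor group size is given, and at ICC 0.01 with small groups uncorrected power stays at or above 80%. This stands: the consequence has to be worded with an if. Type I inflation also needs groups that differ in outcome while the average effect is zero. If the programme and its groups changed nothing for anyone, individual randomisation would hold the error at 5%.

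**The article is condensed and the analysis plan is not shown.** Covariates, site terms or a variance estimator may be fixed there. This stands for the covariate list, whose absence is no fault. It does not reach the sample size, which is stated in full. Nor would an agency covariate suffice, since an agency main effect does not capture group variance arising in one arm.

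**Agency differences.** A reader might infer that leaving out agency also makes the interval too narrow. The documents do not support that. Families appear to be randomised within agencies, so differences shared by both arms cancel from the comparison, and ignoring them tends to widen the interval. Only training-group effects, or treatment effects that differ by facilitator, narrow it.

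**Sharing may be weaker than assumed.** Youth attend four of the eight sessions, the primary outcome is theirs, and one person may not lead both of two parallel groups. Covariate adjustment could also recover some power. These points argue for a small ICC, not for zero.

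**Conclusion.** The concern holds in conditional form. The design is partially nested, the power calculation makes no allowance for it, and the primary model as described assumes independent families. Under any positive within-group correlation the standard error is too small and power is overstated.

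At the assumed 9.8 analysed families per group and ICC 0.01 to 0.05, the loss against no clustering is between 1.5 and 7.6 percentage points of power (81.8 − 80.3 and 81.8 − 74.2), and the naive 5% test runs at 5.5% to 7.6%. These figures rest on the assumed ICC, two equal groups per agency and arm, untrained controls at the primary comparison, and an uncorrected test with pooled null variance.

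A reader might go further and infer that 80% power is certainly missed or that type I error certainly exceeds 5%. The documents do not support that, because they give neither ICC nor group size, and the low end of a reasonable range leaves power at about 80%. The point should be corrected before analysis, but it does not show the trial to be underpowered.

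**What to change.** - Record training-group membership for every intervention family. Under Trial status, four agencies had yet to begin recruiting, so this can still be done prospectively for them.
- Analyse the primary outcome with a method that allows for training-group correlation in the intervention arm only, with control families as singletons. Either a partially nested logistic mixed model, or GEE or cluster-robust variance by training group with a small-sample correction, would serve. Clustering on the seven agencies instead would give unreliable robust standard errors.
- Adjust for agency and baseline susceptibility, for precision.
- Use the same structure for the secondary scales.
- Restate power over an assumed range of ICC and group size, counting analysed families in both the arm and the group.

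**Cost.** No extra families and no new outcome data. The interval will be somewhat wider and the power figure less favourable. With groups of about 10 and 14% susceptible there are only about 10 × 0.14 = 1.4 events per group, so the group variance will be imprecisely estimated. A mixed model also gives a group-specific odds ratio; if the marginal odds ratio is wanted, GEE is preferable.
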